### Outcomes {12}

This study will be conducted as a randomized double-blind placebo-controlled clinical trial to investigate the effects of inulin supplementation on clinical symptoms, inflammatory status, oxidative stress, intestinal permeability, mental health, and QOL in women with migraine. The primary outcome of this study is to evaluate the impact of inulin on the frequency of headaches in women diagnosed with migraines. In addition to this, the study will also focus on secondary outcomes, which include the assessment of serum levels of zonulin, Hs-CRP, total antioxidant capacity (TAC), total oxidant status (TOS), and NO. Furthermore, the mental health status, QOL, duration, and severity of migraine attacks will also be evaluated. The migraine symptoms, such as headache frequency, severity, and duration will be assessed by a neurologist. Participants will then be asked to complete questionnaires regarding the duration and frequency of the attacks during the intervention. The frequency of attacks will be recorded by the monthly incidence of headaches. The severity of pain will be assessed using a visual analogue scale (VAS) ranging from 0 to 10. Participants will be instructed to score 0 if they experience no pain and 10 if they suffer from agonizing pain. The study will measure the following parameters at the baseline and the end of the intervention: levels of zonulin, Hs-CRP, NO, TAC, and TOS, clinical symptoms, mental health status, and QOL. Blood samples will be collected from the patients both before and 12 weeks after the intervention with either inulin or placebo. These samples will be drawn in the morning (8–10 am) under fasting conditions. Following collection, serum will be separated from the blood samples through centrifugation and then aliquoted into 0.5-ml microtubes. The serum samples will subsequently be stored at − 70 °C in a freezer until further analysis.

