### Sample size {14}

The sample size for the present study was calculated based on means and standard deviations for the frequency of attacks, as the main outcome of the study of Ghavami et al. [41], by considering a 95% confidence interval and 80% power (*α* = 0.05 and *β* = 0.2). Frequency of attacks was also considered a main outcome, and based on a previous study, the sample size was calculated as 40 patients for each group. All patients who meet the inclusion criteria and are willing to participate in the trial will be included until the estimated sample size is completed.

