### Assignment of interventions: allocation

#### Sequence generation {16a}

The present study will be conducted as a randomized double-blind, placebo-controlled study using a stratified randomization method. Stratified permuted block randomization will be employed to balance age (20–35 and 35–50 years) between the two groups over time. Within each of the aforementioned strata, eligible patients will be randomly assigned in a 1:1 ratio to receive either inulin or placebo with a block size of four. A block size of four will be constructed in six different arrangements (blocks) which will be created for each stratum to assign patients to the trial groups. The sequence of these blocks will be generated for each stratum using a random number generator available at randomizer.org. A person not involved in the study will randomly divide patients into two groups: intervention (inulin, *n* = 40) and control (placebo, *n* = 40).

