### Statistical methods

#### Statistical methods for primary and secondary outcomes {20a}

Statistical analyses will be conducted using SPSS (version 21.0) software. A *P*-value < 0.05 will be considered statistically significant. The one-sample Kolmogorov–Smirnov test will be used to evaluate the normality of the distribution of data. Regarding missing values, the data analysis will be subjected to intention-to-treat (ITT) analysis. We will employ the multiple imputation approach to perform ITT. In order to compare the baseline value of qualitative and quantitative variables, the chi-square test and *t*-test will be used. Categorical variables will be expressed as number and percentage, while quantitative data will be presented as mean ± standard deviation. Between-group differences will be evaluated using a Mann–Whitney *U* test and independent *t*-test. Differences within the group will also be assessed with a Wilcoxon rank-sum test and paired *t*-test. To control for confounders, an analysis of covariance (ANCOVA) will be carried out.

The primary results of this study include the evaluation of clinical symptoms of patients, such as headache frequency, duration, and severity. The secondary results encompass the evaluation of the serum levels of zonulin, Hs-CRP, TAC, TOS, NO, mental health status, and QOL by questionnaire.

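### The within-group comparison names the Wilcoxon rank-sum test, an independent-samples test, for paired data; the signed-rank test was probably meant (wrong as written, minor)

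*Protocol article*

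**What the plan says.** Under Statistical methods for primary and secondary outcomes {20a}, the protocol article names a rank test beside a t-test for each kind of comparison. For the two arms: "Between-group differences will be evaluated using a Mann–Whitney" U test and an independent t-test. For change inside an arm: "Differences within the group will also be assessed with a Wilcoxon rank-sum test" and a paired t-test. A one-sample Kolmogorov–Smirnov test of normality comes earlier in the same paragraph, presumably to choose between the two tests, although the text does not say so. The threshold is a P-"value < 0.05 will be considered statistically significant".

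Outcomes {12} fixes the data structure: "The study will measure the following parameters at the baseline and the end of the intervention", followed by a list covering the biomarkers, clinical symptoms, mental health and quality of life. For the laboratory markers: "Blood samples will be collected from the patients both before and 12 weeks after the intervention with either inulin or placebo". Table 1 and the section on migraine symptoms assessment show the same two time points. The signed-rank test is not named anywhere in the article.

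**The concern.** Within-group change sets each woman's 12-week value against her own baseline. The rank-sum test treats the two sets of values as coming from different people and discards the link between them. As printed, one independent-samples test appears under two names for two different purposes. In the within-group sentence it is offered as the non-parametric partner of a paired t-test, which it is not.

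What is at stake is limited to the non-parametric within-group P-values. An analyst who followed the text would run a test that often misses real change over time, and a reader of the results could not tell which Wilcoxon test had been used.

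**Working it through.** **Inputs from the protocol article.** Pairs per within-group test: 40, from Sample size {14} ("the sample size was calculated as 40 patients for each group"). Significance level: 0.05, from {20a}; two-sided is assumed because sidedness is not stated. Two measurements per woman: Outcomes {12}. The article states no figure of its own on this point, so there is none to reproduce.

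**Assumed inputs.** The documents give neither the correlation ρ between baseline and 12-week values nor an expected within-group shift. I take ρ from 0 to 0.9 and shifts of 0.3 and 0.5 SD.

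**Step 1: the two names are one test.** On one simulated data set, the rank-sum and Mann–Whitney tests (normal approximation, no continuity correction) both gave P = 0.8399.

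**Step 2: large-sample type I error of the rank-sum test on paired data.** Pairing multiplies the variance of the rank-sum statistic by about 1 − ρs, where ρs = (6/π)·arcsin(ρ/2) for bivariate normal data. The test still uses the variance for independent samples, so its actual type I error is 2[1 − Φ(1.96/√(1 − ρs))].

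- ρ = 0.3: ρs = 0.288, 1.96/√0.712 = 2.32, type I error 2.0%.
- ρ = 0.5: ρs = 0.483, 1.96/√0.517 = 2.72, type I error 0.6%.
- ρ = 0.7: ρs = 0.683, 1.96/√0.317 = 3.48, type I error 0.05%.

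**Step 3: simulation at the planned size.** 40 bivariate normal pairs, 10,000 runs, two-sided 0.05. Each cell gives rank-sum / signed-rank rejection rates.

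| ρ (assumed) | No change (type I error) | Shift 0.3 SD (power) | Shift 0.5 SD (power) |
|---|---|---|---|
| 0 | 5.2% / 5.3% | 25% / 25% | 57% / 56% |
| 0.3 | 2.1% / 5.0% | 21% / 33% | 58% / 72% |
| 0.5 | 0.8% / 5.1% | 18% / 45% | 60% / 85% |
| 0.7 | 0.1% / 4.3% | 13% / 65% | 64% / 97% |
| 0.9 | 0.0% / 4.6% | 6% / 98% | 71% / 100% |

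The type I column agrees with Step 2. A repeat for ρ of 0.3 to 0.7 gave 2.0% to 0.1% type I error for rank-sum, and 58–63% against 73–98% power at 0.5 SD.

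**Step 4: skewed data.** Variables that reach a rank test are likely to be non-normal, so log-normal pairs were also tried (40 pairs, 3,000 runs, 0.5 SD shift on the log scale). For ρ = 0.3, 0.5 and 0.7, rank-sum type I error was 2.3%, 0.6% and 0.03%. Power was 60% against 66%, 59% against 79%, and 63% against 94%. The direction holds, and the gain from signed-rank is somewhat smaller.

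**The case against.** The best defence is that this is only a naming slip. The same sentence names a paired t-test, and the sentence before it already gives independent-samples comparisons to Mann–Whitney and the independent t-test. The plan plainly separates paired from unpaired comparisons, and naming the same rank test again for the paired case would make no sense. That reading is probably right, and it means one cannot say that pairing will in fact be ignored. It does not make the printed sentence correct, and nothing else in the article corrects it. Nor is this a detail left to an unseen analysis plan: a specific test is stated, and it is the wrong one.

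It can also be said that nothing important hangs on it. This stands. The trial is a parallel two-arm superiority trial, and its treatment comparison uses Mann–Whitney, the independent t-test and ANCOVA. Within-group tests are an addition, and only their non-parametric version is affected.

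Third, the size rests on assumed correlations and shifts. This also stands. At ρ = 0.3 the power gap is 58% against 72% with normal data and only 60% against 66% with log-normal data; at ρ = 0 it vanishes.

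**Conclusion.** Wrong as written, and minor. Taken literally, the non-parametric within-group P-values would be too large. With 40 pairs and an assumed ρ of 0.3 to 0.7, type I error falls to between about 2% and 0.1% instead of 5%, and power for an assumed 0.5 SD shift is about 58–64% against 72–98% with signed-rank under normality.

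Three stronger readings are tempting, and the documents do not support them:

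- **A risk of false-positive findings.** With positive correlation, which is what one expects from repeated measures on the same women, the error is conservative and costs power.
- **Damage to the primary result.** The between-group comparison of headache frequency, the ANCOVA and the sample size do not use this test.
- **Efficacy judged on within-group change.** The article does not say so. Whether within-group results should be labelled descriptive is a separate matter that does not follow from a misnamed test.

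**What to change.** In Statistical methods for primary and secondary outcomes {20a}, in the sentence on within-group differences, replace Wilcoxon rank-sum test with Wilcoxon signed-rank test. On 40 pairs the signed-rank test held a type I error of 4.3% to 5.3% at every correlation tried with normal data. The cost is one word; the sample size, data collection and all other analyses stay as they are.

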**Methods:**

This is a randomized, double-blind, placebo-controlled clinical trial involving 80 women with migraine who meet the inclusion criteria (aged between 20 and 50 years with a diagnosis of migraine by a neurologist based on the ICDH-3). Participants will be assigned to receive a daily dose of 10 g of inulin for 12 weeks (intervention group, *n* = 40) or 10 g of maltodextrin as a placebo for the same duration (control group, *n* = 40). The primary outcome will measure the variations in the frequency of headache experienced by the patients. Secondary outcomes will encompass serum levels of zonulin, high-sensitive C-reactive protein, total antioxidant capacity, total oxidant status, nitric oxide, mental status, QOL, duration, and severity of migraine attacks.

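### The protocol does not settle its primary outcome: headache frequency alone in the abstract and Outcomes section, but frequency, duration and severity in the statistics section

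*Protocol article*

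**What the plan says.** Four places in the protocol article bear on which outcome is primary.

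- **Abstract, Methods.** "The primary outcome will measure the variations in the frequency of headache experienced by the patients". The secondary outcomes there include "mental status, QOL, duration, and severity of migraine attacks".
- **Outcomes {12}.** "The primary outcome of this study is to evaluate the impact of inulin on the frequency of headaches in women diagnosed with migraines". The account of the secondary outcomes goes on: "Furthermore, the mental health status, QOL, duration, and severity of migraine attacks will also be evaluated".
- **Sample size {14}.** The calculation uses attack frequency only: "Frequency of attacks was also considered a main outcome", with 40 patients per group at α = 0.05 and 80% power.
- **Statistical methods {20a}.** "The primary results of this study include the evaluation of clinical symptoms of patients, such as headache frequency, duration, and severity". The next sentence reads: "The secondary results encompass the evaluation of the serum levels of zonulin, Hs-CRP, TAC, TOS, NO, mental health status, and QOL by questionnaire". Duration and severity are absent from that secondary list.

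The statistics section gives one general significance threshold, P < 0.05. It does not say how that threshold is to be used if there is more than one primary outcome.

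**The concern.** The section that governs the analysis ranks the outcomes differently from the sections that define them. Duration and severity are secondary in two places and primary in a third. The statistics section also introduces its primary set by example, so its boundary is not firmly drawn.

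At stake is the trial's conclusion. Suppose frequency shows no difference and severity reaches P < 0.05. Under the abstract and Outcomes {12} the primary result is negative; under {20a} it could be reported as positive. The symptoms may well diverge. The Background reports that an earlier 12-week synbiotic trial reduced attack frequency but showed no benefit on severity or duration, while a probiotic trial improved both frequency and severity. If the choice of definition is left until results are known, the 5% error rate of the primary claim is no longer assured.

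**Working it through.** **1. The passages side by side**

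| Place | Frequency | Duration, severity |
|---|---|---|
| Abstract, Methods | primary | secondary |
| Outcomes {12} | primary | listed with the secondary outcomes |
| Sample size {14} | basis of the calculation | not used |
| Statistical methods {20a} | primary | primary, and absent from the secondary list |

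The last row cannot be reconciled with the first two. Both outcomes left one list and entered the other, which is more than loose phrasing.

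**2. The plan's own figure**

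The 40 per group cannot be reproduced, because the article gives no mean difference or standard deviation. It can be inverted. Assuming a two-sided α of 0.05, 80% power and 1:1 allocation, the standardized difference it implies is

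d = (1.960 + 0.842) × √(2/40) = 0.626 (0.634 with the t distribution).

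**3. Error rate if {20a} governs and any one of three counts**

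Inputs: three outcomes (named in {20a}), each tested at 0.05 (the general threshold in {20a}), and success declared on any one (an assumption; no section says so).

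- Independent outcomes: 1 − 0.95³ = 1 − 0.857 = 0.143, or 14.3%.
- Correlated outcomes: P(max|Z| > 1.96) for three normal test statistics with a common correlation, by simulation with 1,000,000 draws. The correlations are assumptions; the documents give none.

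| Assumed correlation | Chance of at least one false positive |
|---|---|
| 0 | 14.3% |
| 0.3 | 13.6% |
| 0.5 | 12.5% |
| 0.7 | 10.9% |
| 0.9 | 8.4% |

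Every value exceeds 5%.

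**4. Error rate if the abstract and Outcomes {12} govern**

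There is one primary test at 0.05, so the rate is 5%.

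**5. Which reading fits the sample size**

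If all three were primary with a Bonferroni split, each would be tested at 0.05/3 = 0.0167. At d = 0.626 and 40 per group, power per outcome falls from 80% to about 66%. Restoring 80% needs n = 2 × (2.394 + 0.842)² / 0.626² ≈ 53.4, that is 54 per group or 108 in total. The planned 80 patients correspond to a single primary test at 0.05, in line with {14}.

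**The case against.** The strongest reply is that frequency is plainly intended as the primary outcome. Three sections point that way, and {20a} may only have meant to introduce the group of clinical measures. That supports the direction of the repair. It does not remove the conflict, because {20a} also restates the secondary list without duration and severity.

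A second reply is that multiplicity handling is commonly left to a statistical analysis plan, which is not shown, and that a journal article condenses. This stands: the absence of a multiplicity rule is not a defect here. But an unseen plan would not undo two conflicting definitions within this document, and nothing about them is a matter of omission.

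Two stronger readings are tempting, and neither is supported.

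- **A reader might infer that the trial fails to keep its 5% error rate.** That requires both the {20a} definition and a rule that any one symptom suffices. No such rule is written, and P < 0.05 is a general threshold, not a decision rule for each outcome.
- **A reader might infer a primary set of seven measures, adding HIT-6, MI, HDR and MHIS from the migraine symptoms section, with an error rate of up to about 30%.** The Table 1 footnote and the quality-of-life section file HIT-6 under quality of life, which {20a} makes secondary. MI, HDR and MHIS are products of frequency, duration and severity, so treating them as independent or equally correlated is the wrong model. In a simulation with 40 per group, t-tests and assumed log-normal values, adding the three products raised the three-outcome rate by only about 1 to 4 percentage points. The Table 1 footnote also lists the clinical features as just frequency, severity and duration. Some openness remains, since the symptoms section calls the derived indices clinical symptoms too, but three is the number {20a} names.

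**Conclusion.** The point holds as an internal contradiction about which result decides the trial, and it needs correcting whatever view is taken of multiplicity. The effect on the error rate is conditional. It is about 11% to 14% if the statistics section governs and any one of three outcomes at P < 0.05 counts as success, for assumed correlations between 0.7 and 0. It is 5% if frequency is the sole primary outcome. The three-outcome count comes from {20a}; the correlations and the any-one rule are assumptions. The sample size is consistent with the single-primary reading, which makes that the natural way to reconcile the text.

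**What to change.** Bring Statistical methods {20a} into line with the abstract, Outcomes {12} and Sample size {14}. For example: *The only primary outcome is headache frequency (attacks per month), compared between groups from baseline to the end of the intervention, and it carries the confirmatory test at P < 0.05. Duration, severity and the derived indices MI, HDR and MHIS are secondary and will be reported as supportive, with confidence intervals.*

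The time frame should follow the document's own measure. The abstract speaks of variation in frequency, and Table 1 places the closing assessment at the start of week 13, so a bare value at week 12 would introduce a new inconsistency. The change should be made and dated before the randomization codes are opened.

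The cost is one sentence, with no change to the 40 per group or to trial conduct. The investigators give up the option of claiming primary success on duration or severity. If they want all three as primary, they would need an explicit multiplicity rule; with a Bonferroni split that means about 66% power per outcome at 40 per group, or 54 per group for 80%, at the effect size the present sample implies.

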#### Interim analyses {21b}

The recruitment of participants for the trial and their engagement in the intervention will be diligently monitored. The continuation criteria will be reviewed periodically throughout the course of the study. An intention-to-treat analysis will be conducted for participants who drop out during treatment sessions or follow-up assessments. It is important to note that participants who drop out will not be excluded from the data analysis. The study will be stopped upon the completion of participant enrollment, provided that no serious adverse events transpire during the course of the study. In the event that adverse events do occur, the study will be promptly discontinued. Adverse events encompass occurrences such as death, disability, and severe allergic reactions that have a substantial impact on the patient’s health. This trial does not include any planned interim analyses.

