#### Intervention description {11a}

Upon recruitment into the trial, patients will be randomly assigned to one of two groups. The intervention group will receive one pack of 10 g inulin (Frutafit® TEX, Sensus; DP ≥ 23) daily for 12 weeks. The control group will receive one placebo pack containing 10 g maltodextrin (Zarfructose Company; dextrose equivalent [DE] = 14) daily. Maltodextrin was chosen as the placebo because it is easily digested and has a similar appearance and taste to inulin. Inulin and placebo will be packed with the same shape, color, weight, and size. A person who is unaware of the study details will label the packs containing inulin and maltodextrin as A or B. Patients will be instructed to continue their usual diet, physical activity, and medications until the intervention is completed. They will also be given instructions on how to use their supplements. Every 4 weeks, patients will receive packs of inulin and a placebo. Additionally, weekly follow-up phone calls and clinic visits will be used to evaluate side effects and treatment compliance.

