#### Strategies to improve adherence to interventions {11c}

Patients will be provided with inulin and placebo packs at weeks 1, 4, and 8. At the baseline, each phone call, and intermediate visits, all patients will receive instructions on how to use their supplements. They will be requested to return the packs with any remaining contents at the end of each 4-week period, and any side effects experienced will be recorded. Additionally, patients will be asked to complete a daily calendar immediately after consuming their assigned treatments. Adherence to intervention refers to the extent to which trial participants’ behavior aligns with their assigned intervention. Adherence to the assigned treatments will be assessed through the use of a daily calendar during each phone call and by counting the returned packs at the end of the trial. Compliance will be calculated using the following formula: Compliance rate = (packs taken / packs prescribed) × 100. A compliance rate below 80% will be classified as poor compliance.

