**Fig. 1 Fig1:**
[figure not shown]
The protocol flow chart and timeline of the study

**Table 1 Tab1:** Schedule of enrollment, intervention, and assessment based on SPIRIT guidelines

		Registration	Allocation	Post-Allocation												Close-out
Time point (week)		-W_1_	W_0_	W_1_	W_2_	W_3_	W_4_	W_5_	W_6_	W_7_	W_8_	W_9_	W_10_	W_11_	W_12_	W_13 (starting)_
Registration	Eligibility testing	*														
	Informed consent	*														
	Randomization		*													
	Allocation		*													
	Patient instruction			*												
Intervention	Supplementation			*	*	*	*	*	*	*	*	*	*	*	*	
	Compliance			*	*	*	*	*	*	*	*	*	*	*	*	
	Adverse events			*	*	*	*	*	*	*	*	*	*	*	*	
Assessment	Demographic			*												*
	Anthropometric indices			*												*
	Physical activity			*												*
	Dietary intake			*												*
	Mental status			*												*
	Quality of life			*												*
	Clinical features			*												*
	Biochemical assays			*												*
	Supplement checklist															*

Demographic variable including: type of migraine (episodic and chronic), age, anthropometric indices, education status (university graduated, and non-university graduated), marital status (single and married), migraine in first relatives, gastrointestinal problems (bloating, constipation and diarrhea), medication (beta-blockers, anticonvulsant drugs, Tricyclic Antidepressants (TCA), Tetracyclic Antidepressant (TeCA), Serotonin-Norepinephrine Reuptake Inhibitor (SNRI) or mixture of them); Anthropometric indices including: body weight (BW), body mass index (BMI) and waist circumference (WC); Mental including: depression, anxiety, stress; Quality of life including: migraine Specific Quality of Life (MSQ) and the headache impact test-6 (HIT-6); Clinical features including: frequency, severity, duration; Biochemical assays including: serum zonulin, High-sensitive C reactive protein (Hs-CRP), total antioxidant capacity (TAC), total oxidant status (TOS), nitric oxide (NO)

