### Data collection and management

#### Plans for assessment and collection of outcomes {18a}

##### Demographic variables

Demographic variables, including the type of migraine (episodic and chronic), age, anthropometric indices (height, body weight (BW), waist circumference (WC), and body mass index (BMI)), education status (university graduated and non-university graduated), marital status (single and married), migraine in first relatives, gastrointestinal problems (bloating, constipation, and diarrhea), medication (beta-blockers, anticonvulsant drugs, tricyclic antidepressants (TCA), tetracyclic antidepressant (TeCA), serotonin–norepinephrine reuptake inhibitor (SNRI)), and physical activity will be obtained from each participant at the initiation and end of the intervention using validated tools.

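### The protocol describes adverse events only by grave examples, against its own side-effect recording, and files bloating, constipation and diarrhoea as demographics instead of a tolerability outcome

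*Protocol article*

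**What the plan says.** Interim analyses {21b} first makes the end of the study conditional on there being no serious adverse events. It then drops the word serious: "In the event that adverse events do occur, the study will be promptly discontinued". The next sentence describes the term: "Adverse events encompass occurrences such as death, disability, and severe allergic reactions that have a substantial impact on the patient’s health". No other section of the article says what an adverse event is.

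Other sections use wider language. Under Intervention description {11a}, "weekly follow-up phone calls and clinic visits will be used to evaluate side effects and treatment compliance". Under Strategies to improve adherence {11c}, packs come back at the end of each 4-week period and "any side effects experienced will be recorded". Data management {19} treats an adverse event as a reason to gather more information before deciding on exclusion, and allows unblinding. Adverse event reporting and harms {22} sends all potential adverse effects to the ethics committee, which acts according to their severity and nature.

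Table 1 has a row labelled "Adverse events", marked weekly. The gut symptoms are elsewhere. Demographic variables, under {18a}, lists "gastrointestinal problems (bloating, constipation, and diarrhea" among items that "will be obtained from each participant at the initiation and end of the intervention using validated tools", and the footnote to Table 1 also places them under demographics.

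**The concern.** The product is a fermentable fibre, and the symptoms that the protocol itself chose to list are bloating, constipation and diarrhoea. If site staff fill the weekly adverse-event row by the only description available, mild or moderate gut symptoms do not belong in it. The stopping sentence adds pressure in the same direction: read literally, an entry of bloating as an adverse event would end the trial.

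What is at stake is the meaning of the safety result. A low adverse-event count could come from the definition and not from good tolerability. The Discussion looks ahead to inulin as an attractive alternative or add-on to current drugs if it proves effective, and readers weighing that will want a tolerability comparison against placebo. The protocol collects the raw material for one, but does not name it as an outcome or say that it will be compared between arms.

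**Working it through.** The protocol states no figure on this point, so the check sets the sections side by side and maps the rows of Table 1.

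**1. What counts as an event, and what follows**

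| Section | Term used | Severity limit | Stated consequence |
|---|---|---|---|
| Interim analyses {21b} | serious adverse events, then adverse events | grave examples only | whole study stopped |
| Intervention description {11a} | side effects | none | evaluated at weekly calls and clinic visits |
| Strategies to improve adherence {11c} | side effects | none | recorded |
| Data management {19} | adverse events | none | information gathered to decide on exclusion; unblinding allowed |
| Adverse event reporting {22} | complications; adverse effects | none; handled by severity | intervention stopped for complications; effects reported, and the ethics committee decides on exclusion or other action |

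The same term cannot mean only study-stopping events in {21b} and also events that lead to a decision about one patient in {19}. If {21b} is right, the procedure in {19} has little to act on, because the study has already stopped. If {19} and {22} are right, {21b} is describing serious adverse events and should say so.

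**2. Table 1, row by row**

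- Supplementation: W1 to W12, 12 marks.
- Adverse events: W1 to W12, 12 marks, the same columns as supplementation.
- Demographic, which contains the gut symptoms: W1 and W13, 2 marks.

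The adverse-event row covers 12 of 12 supplementation weeks. The three gut symptoms are taken at the start and at close-out. Between those points the article states no question specific to them, so they depend on the general side-effect enquiry.

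**3. Link between side effects and the adverse-event row**

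The weekly calls in {11a} and the weekly marks in Table 1 run on the same timetable, so it is natural to think that one feeds the other. No section says so, and the description in {21b} points the other way for anything mild.

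**4. Outcome lists**

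The Abstract, Outcomes {12} and Statistical methods {20a} each list outcomes. None includes gut symptoms or side effects. The section on non-adherence and missing data {20c} promises an account of side effects behind withdrawals, which is not a comparison by arm among all women randomised.

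**The case against.** The strongest case on the other side is that the sentence in {21b} is an illustrative list in a paragraph about stopping the study. On that reading it describes the events that stop the trial, and nothing tells sites to use it for Table 1. The harms section {22} is the proper home for reporting rules, and it is broad. This is a fair reading of the intent, and it lowers the weight of the point. It does not remove it: the sentence uses the unqualified term, it is the only description given, and {19} uses the same term for something else.

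A second objection is that fixed symptom questions and safety tables are commonly left to the full protocol or analysis plan. That stands, and their absence alone is not the point. The conflict between sections and the filing of the symptoms as demographics are both stated in the article.

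Four stronger readings are tempting, and the document does not support them:

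- A reader might infer that gastrointestinal tolerability is not measured. Side effects are evaluated weekly and recorded without a severity threshold, and the three symptoms are taken before and after treatment in both arms. A woman who leaves early is covered by the promise to explain withdrawals in {11b} and {20c}.
- A reader might infer that ending the adverse-event row at W12 leaves a gap. Supplementation also ends at W12, close-out begins at the start of W13, and side effects are recorded with the pack return at the end of each 4-week period, the last included.
- A reader might want a number for the events missed. That would need assumed symptom rates and an assumed way of filling the row, and the protocol gives neither.
- A reader might infer that the cited safety studies of 10 g inulin daily were done in other populations. The article does not describe the populations of those studies.

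**Conclusion.** The point holds in a limited form. The wording in {21b} conflates adverse with serious adverse events and contradicts {11a}, {11c}, {19} and {22}, both on what is recorded and on what follows. If it were applied to Table 1's adverse-event row, it would keep mild gut symptoms out; whether sites would apply it that way is not known. Separately, bloating, constipation and diarrhoea are collected twice in both arms but classed as demographics. During treatment they are captured only through non-specific side-effect recording, and no comparison by arm is stated.

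The size is qualitative: one misworded definition, three sections with inconsistent consequences ({19}, {21b} and {22}), and one symptom group absent from all three outcome lists. It does not affect the primary efficacy analysis. It does limit what the trial can say about tolerability, and it is cheap to correct. The conclusion rests on the article as shown; a fuller protocol could supply the symptom questions, but would not remove the contradiction in this text.

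**What to change.** 1. In {21b}, define an adverse event as any untoward event in a participant of either arm, and label the present examples as serious adverse events.
2. State that side effects found at the weekly calls, clinic visits and pack returns ({11a}, {11c}) are entered in Table 1's adverse-event row.
3. At the weekly calls already scheduled, ask every woman about bloating, constipation and diarrhoea with the same fixed question in both arms.
4. Report the number of women with each symptom by arm as a safety outcome, together with the W1 and W13 items already collected.
5. Reconcile the consequences stated in {19}, {21b} and {22} in the same amendment. If the definition is widened and the stopping sentence left alone, any mild event would literally end the study. Which events should stop treatment or the study is for the investigators and the ethics committee to settle; no rule is proposed here.

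The cost is three short questions in existing calls, one descriptive table, and an amendment by the route in {25}. Prompted questions will raise the count of mild events in both arms, which is a small downside because the comparison with placebo remains fair. Recruitment began on August 21, 2023, so women already on treatment when the amendment takes effect would have the weekly items for only part of their 12 weeks, and the report should give the number of women asked at each week.
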